#### Analyses

Feasibility measures will be reported as numbers and percentages. Baseline characteristics will be calculated for all participants (total), and separately for the intervention and control group. For all quantitative variables the median number and interquartile range (IQR) will be calculated, and for nominal variables the number and percentage distribution will be calculated. Results from physical tests, blood test, body measures, questionnaires, hospitalizations and toxicity-measures will be reported as means and SDs or as median and IQR, as appropriate. Change over time in ordinal categorical values will be evaluated by a trend test using logistic regression. Within-group and between-group differences in continuous-level data will be performed using independent T-tests. Overall and cancer specific survival will be analyzed with the Kaplan-Meier method, competing risk and Cox regression analyses. The significance level of all tests is set at *p* < 0.05 and analyses will be carried out in R by the program’s statistician (AT).

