**Methods:**

PACE-Mobil-PBL is a two-armed randomized controlled trial. Participants will be randomized 1:1 to an intervention group (*N* = 50) or a control group (*N* = 50). Participants in the intervention group will receive standard oncological treatment and a 12-week multimodal intervention, comprised of: (I) supervised exercise training, twice weekly in the hospital setting, (II) home-based walking with step counts and goal-setting, (III) supportive and motivational nurse-led counseling, and (IV) protein supplement after each supervised training session. Participants in the control group will receive standard oncological treatment. The primary outcome is physical function measured by the 30-s chair stand test. Secondary outcomes include measures of feasibility, activity level, physical capacity and strength, symptom burden, quality of life, toxicity to treatment, dose reductions, inflammatory biomarkers, body weight and composition, hospitalizations and survival. Assessments will be conducted at baseline, and after 6, 12 and 16 weeks.

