### Hypothesis

We hypothesize that with a multimodal and exercise-based intervention, participants will maintain physical function. In addition, we believe that participants in the intervention group will have reductions in symptoms and side effects, improved QoL and psychological wellbeing, limited weight loss and muscle wasting, and increased treatment tolerance, compared to participants in the control group.

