#### Patient-Reported Outcome Measures (PROM)

Patient-reported performance status (PRPS) will be assessed using the ECOG performance status [56]. To measure symptom burden, the M.D. Anderson Symptom Inventory (MDASI) version 1 will be used [57]. MDASI is a multi-symptom PROM assessing the severity of symptoms and their interference with daily living [57]. To assess QoL, the European Organisation for Research and Treatment of Cancer Quality of Life Questionnaire C30 (EORTC QLQ-C30) version 3.0 will be applied [58]. The EORTC-QLQ-C30 is designed to be cancer specific, and consists of 30 items distributed throughout different functional and symptom scales [58]. To assess symptoms of depression and anxiety, the Hospital Anxiety and Depression Scale (HADS) version 3.0 will be used [59]. HADS comprises 14 items and is designed to measure general depression and anxiety by self-administration [59].

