#### Treatment tolerance and toxicity

Data on dose-reductions and treatment discontinuations will be registered prospectively throughout the intervention period. Toxicity will be registered according to the NCI CTCAE v4.0.

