### Statistics

#### Sample size

No prior studies have investigated the clinically important difference in the 30s-CST in patients with cancer. According to a previous study focusing on patients with osteoarthritis, the clinically important change in the 30s-CST was set at 2.6 repetitions [60]. Based on results from prior studies in patients with advanced cancer, a standard deviation (SD) of approximately 3 has been reported [61, 62]. To be able to detect a between-group difference in the within-group changes of 2.6 repetitions in the 30s-CST, and to obtain a type I error rate of 5% and a power of 90%, a sample size of 29 participants per study arm will be needed. To account for a dropout rate of approximately 40%, it has been decided to increase the group size to 50. Thus, a total of 100 participants will be included in the trial.

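### For ordinal outcomes the article names only a test of change over time and no comparison of the arms, although its hypotheses are comparisons with control

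*Protocol article*

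**What the plan says.** All references are to the protocol article.

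- **Analyses**, ordinal outcomes: "Change over time in ordinal categorical values will be evaluated by a trend test using logistic regression". The model terms are not described.
- **Analyses**, the sentence that follows: "Within-group and between-group differences in continuous-level data will be performed using independent T-tests". This is the only place in the section where a between-group test is assigned to a type of outcome other than survival.
- **Analyses**, reporting: physical tests, blood tests, body measures, questionnaires, hospitalisations and toxicity measures are summarised by mean and SD or by median and IQR.
- **Hypothesis**: the expected benefits include "increased treatment tolerance, compared to participants in the control group", and symptoms, side effects and quality of life are framed in the same way.
- **Study outcome measures**: patient-reported performance status, and treatment tolerance and toxicity, are both listed as secondary endpoints.
- **Patient-Reported Outcome Measures (PROM)**: "Patient-reported performance status (PRPS) will be assessed using the ECOG performance status".
- **Treatment tolerance and toxicity**: "Toxicity will be registered according to the NCI CTCAE v4.0".
- **Abstract, Methods**: "Assessments will be conducted at baseline, and after 6, 12 and 16 weeks". Table 2 marks performance status at four time points and has toxicity recorded at each treatment course.

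**The concern.** The two adjacent sentences in the Analyses section divide the work: continuous outcomes get a between-group test and ordinal outcomes get a time trend. Followed literally, patient-reported performance status is tested for whether it drifts over 16 weeks, not for whether the arms differ.

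Patients with advanced cancer on first-line palliative treatment may well change over that period whatever arm they are in. A significant trend would not show benefit, and a flat one would not show its absence. The gain from randomising is lost for this endpoint.

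A second, smaller matter goes with it. Each participant contributes up to four scores, which are correlated, and the section names no method for that. It matters once an arm comparison is written in, because the obvious shortcut of adding an arm term to an ordinary logistic model over all records can give too many false positives.

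**Working it through.** **1. The plan's own figure.** The only sample-size calculation concerns the primary outcome, the 30-s chair stand test: difference 2.6, SD 3, alpha 5% (two-sided assumed), power 90%. The normal approximation gives n = 2 × (1.960 + 1.282)² × 3² / 2.6² ≈ 28 per arm. The t-based calculation gives 28.97, so 29, as stated. Allowing for 40% dropout, 29 / 0.60 = 48.3, so 49; the article uses 50. The figure reproduces and has no bearing on ordinal outcomes, for which the article gives no figure.

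**2. What a time trend estimates.** Let the log-odds of a worse category change by β per unit of time in the control arm and by β + γ in the intervention arm. The intervention effect on the course is γ. With 1:1 allocation, a trend fitted to everyone estimates roughly β + γ/2.

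- If γ = 0 and β ≠ 0, there is no intervention effect, yet the trend test tends to reject.
- If γ = −2β, the arms move in opposite directions, yet the pooled trend is about zero.

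Running the trend test separately in each arm does not help: it tests β and β + γ each against zero, and never γ.

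**3. Which outcomes are covered.** Patient-reported ECOG status is clearly ordinal and repeated. CTCAE grade is ordinal by construction, but the article does not assign it to this test and lists toxicity measures among the results to be summarised. It is covered only if it is analysed as ordinal. Dose reductions and treatment discontinuations are events or counts and are not covered.

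**4. If the correlation were ignored.** This is conditional, since the article does not say that it is ignored. Assumptions, none from the article: a two-category split of the scale, visits at 0, 6, 12 and 16 weeks, no true effect, no missing visits, and a participant random intercept with SD 0 to 3 on the logit scale. The latent intraclass correlation is SD² / (SD² + π²/3). An ordinary logistic model is fitted to all records, with 3,000 runs per setting and a nominal level of 5%. N is the total over both arms.

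| SD | Latent ICC | Time trend, N = 60 | Time trend, N = 100 | Pooled arm effect, N = 60 | Pooled arm effect, N = 100 |
|---|---|---|---|---|---|
| 0 | 0 | 5.4% | 4.3% | 4.4% | 4.9% |
| 1 | 0.23 | 3.2% | 3.0% | 10.4% | 11.9% |
| 2 | 0.55 | 1.0% | 1.5% | 17.5% | 18.4% |
| 3 | 0.73 | 0.3% | 0.5% | 21.8% | 22.4% |

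A naive arm-by-time term behaves like the trend. At SD 1, 2 and 3 it rejects in 2.7%, 1.7% and 0.5% of runs with N = 60 and in 2.8%, 1.1% and 0.3% with N = 100 (2,000 runs). A repeat of all three contrasts with a fresh random seed gave the same pattern. The direction of the error therefore depends on the contrast: within-person contrasts become conservative and the pooled between-person contrast anti-conservative.

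**The case against.** The strongest reply is that one sentence in a journal article is being asked to carry too much. Several things that a reader might infer from it are not there.

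- **That repeated visits are treated as independent.** The article is silent. Logistic models can carry random effects, GEE or robust standard errors, and an article commonly leaves that detail to the full protocol or analysis plan. The use of independent t-tests for within-group differences in the next sentence makes the question natural, but does not answer it for ordinal data.
- **That the scale is cut in two.** Not stated. Cumulative-logit regression is also logistic regression and fits the wording.
- **That the arms are never compared.** Also too strong. The model could contain an arm or arm-by-time term, or the trend could run across ordered categories of change with arm as the response. The article simply names no such comparison.
- **That the toxicity and tolerance hypotheses as a whole lack a test because of this sentence.** CTCAE grade is not assigned to it, and dose reductions are not ordinal.
- **That false positives run at two to four times the nominal level.** That applies to a pooled arm model that the article does not propose, at correlations that it does not give. The trend that it does state would, if fitted naively, err towards too few false positives.

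All of this stands and limits the point. What remains is not a missing detail. The article does state a method for ordinal outcomes; the target that it states is change over time, and it names between-group testing for another class of data. That does not match its own hypotheses.

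**Conclusion.** The point holds in this limited form. For ordinal outcomes the article specifies a test whose stated target is change over time and names no contrast between the arms, while its hypotheses and secondary endpoints call for one. The outcome certainly affected is patient-reported ECOG performance status; CTCAE grade is affected only if it is analysed as ordinal.

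No single size can be put on the mismatch: a time trend and an arm effect are different quantities. The simulated error rates only show why the handling of correlation should be written down together with the arm contrast. They depend on the assumed random-intercept SDs and the two-category split, and do not describe what the trial will do.

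The primary outcome, its analysis and the sample size are unaffected. The change is worth making before analysis because it is cheap and gives this endpoint a randomised comparison.

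**What to change.** Replace the sentence on ordinal outcomes with a model that estimates the arm effect. Either of these would serve:

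- a proportional-odds (cumulative-logit) mixed model with a participant random effect; or
- ordinal GEE with robust standard errors clustered on participant.

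Include arm, visit, arm-by-visit, the baseline category where it was measured, and diagnosis, which is the stratification factor under Randomization. With baseline as a covariate, the modelled responses are the assessments after 6, 12 and 16 weeks. Report the between-arm odds ratio with its 95% confidence interval at the post-intervention assessment. Say which type of model is used, since the mixed-model odds ratio is conditional on the participant and the GEE odds ratio is a population average. The change over time within each arm can be kept as description.

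State also whether CTCAE grade is to be analysed in this way or only summarised.

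The cost is a few lines of text and modest extra R code. No assessment, data item or participant is added.

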### Randomization

After inclusion and baseline assessments, participants are randomly allocated to the intervention group or the control group using a 1:1 block randomization. The block size will only be known by the statistician carrying out the randomization procedure. Randomization will be stratified on diagnosis by using separate randomization lists for each diagnosis group (PC, BTC and LC). The ‘blockrand’ package of the statistical software R was used to generate all randomization lists. Randomization will be administered via the web-based research platform REDCap (Research Electronic Data Capture). Source codes to generate all randomization lists are stored to ensure full reproducibility.

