### Study outcome measures

The primary endpoint is the between-group difference in within-group changes in physical capacity and lower extremity strength measured with the 30-s chair stand test (30s-CST) at the post-intervention assessment. Secondary endpoints include feasibility measures, adverse events, and changes in functional performance, muscle strength, body composition, body weight, patient-reported performance status, symptom burden, symptoms of depression and anxiety, QoL, physical activity, treatment tolerance and toxicity, inflammatory biomarkers, hospital admissions and mortality. The outcome measures for both groups are described in the following section.

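### Adjusting the primary 30s-CST comparison for baseline score and diagnosis would gain precision at no cost; the stated sample size is unaffected

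*Protocol article*

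**What the plan says.** - **Endpoint** (Protocol article, Study outcome measures): "The primary endpoint is the between-group difference in within-group changes in physical capacity and lower extremity strength". The instrument is the 30s-CST, assessed after the intervention.
- **Analysis** (Analyses): "Within-group and between-group differences in continuous-level data will be performed using independent T-tests". No covariate is named, and no other method is given for continuous outcomes. Survival, by contrast, gets a regression model.
- **Allocation** (Randomization): "participants are randomly allocated to the intervention group or the control group using a 1:1 block randomization", with a separate list for each of pancreatic, biliary tract and lung cancer.
- **Baseline** (Participants; Table 2): the 30s-CST is measured before randomisation.
- **Sample size** (Sample size): the target is a "between-group difference in the within-group changes of 2.6 repetitions in the 30s-CST" at 5% type I error and 90% power. For variability, "a standard deviation (SD) of approximately 3 has been reported" in advanced cancer. The text does not say whether that is the SD of change or of scores at one visit. It needs 29 per arm, raised to 50 for about 40% dropout.

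**The concern.** A change score fixes the coefficient on baseline at 1. Where the correlation between visits is below 1 and the variances are similar, the best-fitting slope is smaller. The change score then over-corrects: an arm that happens to start low tends to show more improvement through regression to the mean. The t-test also leaves the variation between diagnosis groups in its error term, although allocation has largely removed that variation from the comparison of arms.

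At stake is the precision of the primary estimate with about 30 evaluable participants per arm. It matters more because the 2.6-repetition target comes from osteoarthritis, and the article says no such value exists for cancer. A smaller true effect is therefore plausible, and there the margin in power is thinner.

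**Working it through.** **Inputs from the document.** Difference 2.6, SD 3, alpha 0.05 (taken as two-sided), power 0.90, 29 per arm, 50 per arm randomised, about 40% dropout.

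**Assumptions, not in the document.** Correlation r between baseline and follow-up 30s-CST; equal variance at both visits; the share of outcome variance explained by diagnosis.

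**1. The plan's own figure.** Two-sample t-test (noncentral t), difference 2.6, SD of change 3:
- 29 per arm: power 0.900. The stated N reproduces.
- 50 × (1 − 0.40) = 30 evaluable per arm: power 0.910.

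No correlation enters this calculation.

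**2. Gain from baseline adjustment, with 3 as the SD of change.** The residual variance of the adjusted model is (1 + r)/2 times the change-score variance.
- r = 0.5: factor 0.75 (25% lower); SD = 3 × √0.75 = 2.60.
- r = 0.7: factor 0.85 (15% lower); SD = 3 × √0.85 = 2.77.

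Power at 30 per arm:

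| True difference | t-test on change | Adjusted, r = 0.7 | Adjusted, r = 0.5 |
|---|---|---|---|
| 2.6 | 0.91 | 0.95 | 0.97 |
| 2.0 | 0.72 | 0.79 | 0.83 |

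Charging three degrees of freedom for baseline and two stratum terms leaves these values unchanged to two decimals.

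**3. Chance baseline imbalance.** At r = 0.5 a change SD of 3 corresponds to a single-visit SD of 3, because 3 × √(2 × 0.5) = 3. The standard error of the baseline difference at 30 per arm is 3 × √(2/30) = 0.77 repetitions. An imbalance of that size shifts the change-score estimate by (1 − 0.5) × 0.77 = 0.39 repetitions, and 0.39/2.6 = 15% of the target difference.

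**4. Ignoring the stratum.** If diagnosis explains a share R² of the variance and balance is kept, the t-test's standard error is too large by 1/√(1 − R²).
- R² = 5%: 1.03; R² = 15%: 1.08.
- With balance fully kept among those analysed, true alpha would be about 4.4% and 3.4%.
- Dropout partly breaks that balance. Simulating 100 randomised participants, three strata of similar size and 40% random dropout gives about 4.7% and 4.1%.

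**5. If 3 is instead a single-visit SD.** The SD of change is 3 × √(2(1 − r)). Power of the planned t-test at 29 per arm:

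| r | SD of change | Power |
|---|---|---|
| 0.3 | 3.55 | 0.78 |
| 0.5 | 3.00 | 0.90 |
| 0.6 | 2.68 | 0.95 |
| 0.7 | 2.32 | 0.99 |

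The planned test misses 90% only on this reading and only with r below 0.5.

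**The case against.** The strongest reply is that the plan is coherent. Endpoint, sample size and test all concern a difference in changes, and the stated N follows from them exactly. A t-test on change scores is unbiased over randomisation. Chance baseline imbalance is random error that the change-score variance already counts. Omitting a prognostic stratum makes the test conservative, so it does not add false positives. The article is also condensed: one sentence covers all continuous data, and it does not rule out an adjusted model in a fuller plan.

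Most of this stands. It removes any charge of invalidity and any charge against the sample size. It does not remove the point, because the article states a method rather than leaving it open, and that method sets aside information the trial already collects.

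Three stronger readings are tempting, and the document supports none of them:
- *The 90% power rests on an unstated correlation.* The calculation is framed as a difference in changes and reproduces with 3 as the SD of change. A shortfall needs both a single-visit SD and r below 0.5; at r of 0.5 to 0.7 there is none on either reading.
- *Adjustment guarantees 90% whichever SD was meant.* That needs equal variances. With a baseline SD of 3, a follow-up SD of 3.5 and r = 0.3, the residual SD is 3.5 × √(1 − 0.09) = 3.34, and power at 30 per arm is about 0.84.
- *Ignoring the stratum pulls alpha down to 3.4%.* That holds only if dropout leaves the strata balanced between arms.

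**Conclusion.** The point holds as a free improvement. The planned t-test is valid and matches its sample size, but it is less precise than the trial's own data allow. If variances are equal at both visits and r is 0.5 to 0.7, baseline adjustment removes 25% to 15% of the variance. At 30 per arm that is worth about 4 to 6 percentage points of power at 2.6 repetitions and 7 to 11 at 2.0. The gain shrinks as r approaches 1.

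The effect of ignoring diagnosis is small and conservative: true alpha about 4.7% to 4.1% if diagnosis explains 5% to 15% of the variance and 40% drop out at random. The document gives neither r nor the share due to diagnosis, so these ranges are illustrations. The unlabelled SD is worth clarifying, but it does not show the stated power to be wrong.

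**What to change.** In Analyses, name as the primary analysis a linear model of post-intervention 30s-CST on arm, baseline 30s-CST and diagnosis stratum (pancreatic, biliary tract, lung). Report the adjusted mean difference with its 95% confidence interval. Use the same form for the other continuous between-group comparisons that have a baseline value, and keep the unadjusted t-test on change as a sensitivity analysis. In Sample size, add a few words saying whether the SD of about 3 refers to change or to a single visit.

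The cost is a sentence or two, settled before the outcome data are analysed. No extra participants, visits or measurements are needed, and the sample size stays at 100.

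### The protocol assigns independent t-tests to within-group changes, which are paired measurements; with positive correlation between visits, the secondary within-group p-values are too large and the intervals too wide

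*Protocol article*

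**What the plan says.** The only test that the article names for continuous outcomes is in Statistics, Analyses: "Within-group and between-group differences in continuous-level data" "will be performed using independent T-tests". One test is thus given to two different comparisons. No paired test, repeated-measures model or other within-group method for continuous data appears elsewhere in the article.

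Table 2 (schedule of study assessments) has the same participants measured at baseline and again at later visits on the chair stand test, walking and gait tests, handgrip, body weight, body composition and questionnaires.

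The primary endpoint is a between-group contrast (Study outcome measures): "The primary endpoint is the between-group difference in within-group changes in physical capacity and lower extremity strength". The sample size is built on the same contrast: "To be able to detect a between-group difference in the within-group changes of 2.6 repetitions in the 30s-CST". The SD behind it is described only as follows: "a standard deviation (SD) of approximately 3 has been reported". The article does not say whether this is the SD of a score or of a change, and it gives no correlation between visits.

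**The concern.** An independent-samples t-test assumes two unrelated samples. That holds between the arms and fails within an arm, where each follow-up value belongs to a person who also supplied a baseline value. When the two values are positively correlated, the variance of the mean change is smaller than the test assumes. The test then overstates the standard error, so p-values are too large, intervals are too wide, and real changes within an arm go undetected more often than they should.

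At stake are the within-group results for all continuous outcomes. The same section sets a 0.05 significance level for all tests, so these would be reported as formal tests. The article names a method, and the method does not fit the data. This is therefore not a detail left to an analysis plan that is not shown.

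**Working it through.** **1. The plan's own figure.** For a between-group difference in change of 2.6, SD 3, two-sided 5% and 90% power, the normal approximation gives 2 × 3² × (1.960 + 1.282)² / 2.6² ≈ 28 per arm. The exact two-sample t calculation gives power 0.890 at 28 and 0.900 at 29, so the stated 29 is reproduced. Allowing for 40% dropout, 29 / 0.6 = 48.3, which rounds up to 49; the plan uses 50. This calculation is for the between-group test of changes, for which the independent t-test is valid. Nothing below alters it.

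**2. Inputs for the within-group check.** Completers per arm: 50 × (1 − 0.40) = 30. SD: 3 (Sample size), taken in turn as the SD of a score at one visit and as the SD of a change. Correlation r: an assumption, range 0.3 to 0.8. Scores are taken as bivariate normal with equal SD s at both visits.

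**3. Standard errors.**

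- Independent test: s × √(2/n)
- Paired test: s × √(2(1 − r)/n)
- Ratio: 1/√(1 − r), which is 1.20 at r = 0.3, 1.41 at 0.5, 1.83 at 0.7 and 2.24 at 0.8

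At r = 0.7 and n = 30:

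- Score SD 3: 3 × √(2/30) = 0.775 against 3 × √(0.6/30) = 0.424.
- Change SD 3: the visit SD is 3/√(2 × 0.3) = 3.87, so 3.87 × √(2/30) = 1.00 against 3/√30 = 0.548.

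The larger degrees of freedom of the independent test (58 against 29) narrow its interval by only about 2%.

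**4. Actual type I error of the independent test at nominal 5%** (simulation, n = 30; the paired test stays at about 5% throughout):

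| r | Actual type I error |
|---|---|
| 0 | about 5% |
| 0.3 | about 2% |
| 0.5 | about 0.7% |
| 0.7 | about 0.07% (runs from 0.06% to 0.08%) |
| 0.8 | below 0.01% |

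**5. Chance of detecting a true within-group decline** (simulation, n = 30, r = 0.7):

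| Decline (repetitions) | Score SD 3: paired | Score SD 3: independent | Change SD 3: paired | Change SD 3: independent |
|---|---|---|---|---|
| 1 | 63% | 12% | 42% | 5% |
| 1.5 | 93% | 47% | 75% | 20% |
| 2 | above 99% | 84% | 94% | 51% |
| 2.6 | 100% | 99% | 99.5% | 85% |

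At r = 0.5 the two readings of the SD coincide: a decline of 1 is detected 17% of the time against 42% with the paired test, and a decline of 2.6 is detected 97% against more than 99%. At r = 0.8 with change SD 3, even a decline of 2.6 is detected only about 60% of the time, against 99.5%.

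**The case against.** The strongest reply is that nothing confirmatory depends on this. The primary endpoint and the sample size both concern the difference between arms in change, for which an independent t-test on change scores is valid, and no within-group test is named as an endpoint. That stands, and it limits the point to secondary results.

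A second reply is that the sentence is a compressed version of the phrase used for the primary endpoint and means only between-group tests of within-group changes. This is plausible in a condensed article. But the sentence lists within-group and between-group differences as two items, and an analyst who follows it literally would run the wrong test. If the benign meaning was intended, the wording still needs correcting.

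Third, the size is conditional. At r = 0 the two tests nearly agree, and for positive r the error is conservative: it loses power and creates no excess of false positives. The largest losses are at declines below 2.6 repetitions, the change that the plan treats as clinically important. At 2.6, with score SD 3 and r = 0.7, the independent test still detects 99%. All of this stands, and it is why a range is given.

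A reader might go further and infer that a real decline would be reported as preserved function, because the Hypothesis section says: "We hypothesize that with a multimodal and exercise-based intervention, participants will maintain physical function". The article does not support that. It states no rule by which a non-significant within-group test would count as maintenance, and the primary endpoint is comparative. A non-significant paired test would not demonstrate maintenance either, so that is a separate matter from the choice of test.

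**Conclusion.** The point holds as an error in the stated analysis of within-group change and should be fixed. For any positive correlation between visits, within-group p-values are too large and intervals too wide, by a factor of about 1.2 to 2.2 over r = 0.3 to 0.8. The loss of power is large for declines of 1 to 2 repetitions once r reaches 0.5. For 2.6 repetitions it ranges from negligible to substantial, depending on r and on whether the SD of 3 refers to scores or to changes.

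These figures assume 30 participants per arm with both visits, normal scores, equal SD at the two visits, and a correlation that the article does not state. It would go too far to say that every within-group result is wrong whatever the correlation, or that the trial's main conclusion is at risk: the primary comparison and the 50 per arm are untouched.

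**What to change.** In Statistics, Analyses, split the sentence in two. For within-group change in continuous outcomes, name paired t-tests, or visit contrasts from a repeated-measures model, reported with 95% confidence intervals. For between-group differences in change, keep the independent t-test. Add one sentence saying that the effect of the intervention is judged only on the between-group difference and that within-group changes are descriptive.

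The cost is wording only: no new data, no extra assessments and no change to the sample size.
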